### Data collection and management

De-identified data will be extracted from Epic (the electronic medical record) from March 17, 2020, to March 16, 2021, then every 6 months from March 17, 2021, until September 17, 2025. The study timeline is depicted in a SPIRIT diagram in Fig. 3. Data extraction will be performed by Health Data Compass, the Colorado Center for Personalized Medicine’s cloud-based enterprise data warehouse and management platform. Health Data Compass extracts de-identified data using a proprietary process, wherein all data are checked for process compliance and missingness prior to release to the study team. As these data are de-identified, informed consent was not utilized. However, a written informed consent process was utilized for specified, individually contacted patients and practice members for the purposes of the implementation evaluation.

**Fig. 3 Fig3:**
[figure not shown]
SPIRIT diagram

Retrospective data will be collected on all patient encounters at the 57 primary care clinics at the specified times described above. Specifically, how many patient visits occurred at each clinic, how many discrete patients were seen at each clinic, how many patients were ≥18 years old with a BMI ≥ 25 kg/m^2^, and how many patients who were ≥18 years old with a BMI ≥25 kg/m^2^ had a weight-prioritized visit (either in person or by telehealth). These data will be illustrated in an Expanded CONSORT diagram [31]. Data will be stored on a secure data server with access provided to the study statisticians. The statisticians will not be blinded to the assignment of the interventions.

### Sample size

A conservative sample size estimate is 6840 total patients (120 patients per clinic from 57 clinics) that assume a minimum of 30 eligible patients per clinic per year based on the smallest clinic. We present the power calculations assuming an intraclass correlation coefficient (ICC) between 0.02 and 0.05. With this design, we will have 80% power (alpha=0.05, two-sided) to detect a standardized effect size of 0.118 (ICC=0.02) to 0.121 (ICC=0.05). For our primary effectiveness outcomes, we estimate a standard deviation (SD) of 10.1 percentage points for percentage change in weight using our pilot study, and a similar SD estimate of 10.7 for absolute (kg) change in weight. Thus, with 80% power we can detect a mean difference in weight change of 1.19 (ICC=0.02) to 1.22 (ICC=0.05) percentage points between the control and intervention conditions, and a mean difference in absolute weight change of 1.26 kg (ICC=0.02) to 1.29 kg (ICC=0.05).

### Interventions

#### Current standard of care (SOC)

SOC will be the control condition that patients will receive during the control phases of the design. Clinics in the SOC condition will conduct visits in which weight may be discussed (defined as “weight-prioritized” for purposes of data extraction) without access to either the PATHWEIGH tools in Epic or the PATHWEIGH implementation strategies. Current SOC for obesity in the primary care clinics is called “obesity – brief history of present illness (HPI),” and the option to select “Obesity brief HPI” is currently available to all Epic users at all practices. For an example of the Obesity brief HPI questionnaires, see Additional File Fig. S1. For a weight prioritized visit, this entails a brief historical intake of a patient’s weight and is intended to initiate a discussion regarding potential strategies for weight loss. Because SOC can be highly variable, we will conduct fidelity checks by performing sensitivity analyses for the use of the “Obesity brief HPI” in the SOC clinics at our every 6-month data extractions. A change in the use of the “Obesity brief HPI” by more than 30% between 6-month intervals will be investigated. There are currently no systematic weight management interventions at the clinics.

#### PATHWEIGH: Clinical workflow and management

PATHWEIGH is a workflow optimization and management system for weight management built into Epic (Fig. 4). The PATHWEIGH tools in Epic are designed to address numerous barriers to prioritizing weight management in primary care [8]. Once practices transition to receive the intervention, PATHWEIGH will be “turned on” within Epic and the PATHWEIGH implementation strategies will be provided. The key components of PATHWEIGH are summarized in Table 2 and include (1) encouraging patients to schedule a weight-prioritized visit if they would like medical assistance with weight management, (2) improving workflow efficiency around weight-prioritized visits, and (3) clinical decision support during weight-prioritized visits.

**Fig. 4 Fig4:**
[figure not shown]
PATHWEIGH clinic flow

**Table 2 Tab2:** Key components of PATHWEIGH and PATHWEIGH implementation strategies

***PATHWEIGH is a weight management care path built into Epic.*** It includes: • Weight-prioritized visit type: Defines the scope of the visit for the patient and provider. • Time-efficient documentation and data capture: Patient questionnaire completed prior to the visit captures history around weight gain and barriers to weight loss that can guide the patient-clinician conversation and treatment plan. • Clinical decision support: SmartSet in Epic suggests weight loss approach(es) based on patient BMI and preferences according to the Obesity Society guidelines [32]. • Tracking: Displays progress with weight loss and weight loss maintenance during patient visits to guide the patient-clinician conversation and evolving treatment plan over time. • Diagnosis and billing: Tool in Epic automatically adds the diagnosis of overweight (for BMI 25-29.9 kg/m^2^) or obesity (for BMI> 30 kg/m^2^) and links the most common weight-related co-morbidities (according to the Center for Medicare and Medicaid Services) to ensure adequate provider reimbursement.	
***PATHWEIGH implementation strategies*** include: • Practice facilitation: Practice facilitators drive implementation efforts by working with practice-selected Practice Champions, engaging leadership in goal setting and monitoring along system and practice goals, and utilizing quality improvement techniques for supporting adoption, implementation, and management of PATHWEIGH. • Clinician education: Online e-learning module on evidence-based weight management treatment which includes 2 credits of continuing medical education. • Consultation support: built-in to Epic consultation support for clinicians by request; built-in to Epic availability of UpToDate, a subscription-based clinical reference.	

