## Evaluation

### Aim 1: Compare the effectiveness of PATHWEIGH versus standard of care (SOC) on weight loss and weight loss maintenance.

#### Outcomes and Measures

The primary outcome is patient weight between baseline and 6 months in kilograms (kg) as measured by a standard scale. The secondary outcome of weight loss maintenance will be defined at 12 and 18 months as a binary outcome of weight increase ≤ 10% from the patient’s 6-month weight. Weight outcomes will be extracted from the EMR. The primary independent variable will be the intervention status, which will be determined based on visit date and practice sequence. Additional covariate data will be collected from the EMR on potential confounders at the level of patient, provider, and practice. Patient-level data will include demographic information, health metrics, behaviors and goals, and treatment strategy employed. Provider-level data will include demographic information, years practicing, and percent time practicing. Clinic-level data will include site type/discipline, location, and size. Outcomes, measures, and timing of data collection are described in Table 3.

**Table 3 Tab3:** Summary of outcomes, measures, data sources, and timing of collection for PATHWEIGH study

Construct	Metric/measure	Method of collection	Timing

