**Patient-specific outcomes**			
Weight-related outcomes	Weight (kg), height (cm), weight loss maintenance (weight increase ≤ 10%)	EMR	Collected during routine care
Clinical and laboratory values	Thyroid-stimulating hormone (TSH), lipid panel, liver function tests, A1c, blood pressure	EMR	Collected during routine care
Patient characteristics	Demographics (age, gender, race/ethnicity, insurance, comorbidities, medications)	EMR	Collected during routine care

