For the primary analysis, although the parameter of interest is weight change at 6 months, weight collected from baseline to approximately 9 months post-baseline for the individual patient will be included in the primary analysis because patients may not have visits with recorded weight within the 6-month time frame. The mixed model will include random intercepts for patient, provider, and clinic, along with fixed effects for time and intervention condition. The time effects are two-fold: (i) calendar time, divided into four 1-year periods and included as a categorical variable to flexibly model its effect on the outcome and account for temporal trends, and (ii) individual patient time, included as a continuous variable (i.e., time from baseline) to accommodate varying visit times determined by each patient’s visit schedule. The intervention condition variable will be a binary indicator that is equal to zero if the patient’s index visit occurs at a clinic when it is in the control condition and becomes equal to 1 when the patient has an index visit at a clinic after it has crossed into the intervention condition. Patient-, provider-, and practice-level covariates will be included in models if deemed to be potential confounders in univariate models. An additional fixed effect for the interaction between patient time and intervention condition will be used to estimate the parameters of primary interest, i.e., the difference in change in outcomes over time between the intervention and control conditions. The primary analysis will test the null hypothesis that the interaction effect coefficient is equal to zero to determine whether there is a significant difference in weight change between the PATHWEIGH and SOC conditions. Using the model, we will report the mean weight change in the control and intervention groups and their difference at 6 months, with corresponding 95% confidence intervals and *p* values.

To examine the secondary binary outcomes of weight maintenance (defined as < 10% weight gain at 12 and 18 months), we will use generalized linear mixed models. Since this analysis will involve a single outcome per patient, the model will only include a random intercept for provider and clinic. The test of intervention effectiveness will be captured by the fixed effect term for the intervention condition.

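### Aim 1 confounders are screened from EMR fields that PATHWEIGH itself helps to fill, with no pre-index or equal-capture rule; this can bias the 12- and 18-month maintenance tests

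*Protocol article*

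**What the plan says.** **What the intervention records.** Table 2 of the protocol article says the Epic tool adds the overweight or obesity diagnosis automatically and "links the most common weight-related co-morbidities (according to the Center for Medicare and Medicaid Services) to ensure adequate provider reimbursement". Under Staff workflow and Clinician workflow, patients are asked for a weight questionnaire at e-check-in, and the SmartSet carries the answers into the documentation. Use of the tools is optional. Under Current standard of care (SOC), control clinics lack these tools and have the Obesity brief HPI.

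**What may be adjusted for.** Aim 1, Outcomes and Measures, says covariates on potential confounders come from the EMR, and continues: "Patient-level data will include demographic information, health metrics, behaviors and goals, and treatment strategy employed". Table 3 lists "Demographics (age, gender, race/ethnicity, insurance, comorbidities, medications" as EMR data from routine care, with no date limit.

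**How covariates are chosen.** Aim 1, Analysis: "Patient-, provider-, and practice-level covariates will be included in models if deemed to be potential confounders in univariate models".

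**What is tested.** The primary test is the patient time by intervention interaction, in a model with a patient random intercept. The maintenance models have one outcome per patient and test the intervention main effect.

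**The one safeguard.** Aim 2, Analysis, restricts clinic- and provider-level mediators to those obtainable from the EMR in both phases. Aim 1 covariates have no such rule.

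**The concern.** A confounder should describe the patient, not the recording system. Here the intervention can change how completely a trait is recorded at the index visit. Two identical patients may then carry different covariate values because one clinic had the tool switched on.

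Univariate screening makes this worse. A field filled more often in one condition looks imbalanced, which is one of the marks by which a confounder is recognized, so the screen tends to admit it. Adjustment then compares unlike groups: under SOC, the patients with nothing recorded include many unrecorded cases; under PATHWEIGH, few.

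Treatment strategy is a plainer problem in the same list. It follows the intervention, and Aim 2 itself treats prescribed treatment as a mediator. Adjusting for it would remove part of the effect under test.

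At stake are the two named secondary outcomes, whose test is a between-condition main effect.

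**Working it through.** **1. The plan's own figure, used only as a yardstick.** Inputs from Sample size: "6840 total patients (120 patients per clinic from 57 clinics", "a minimum of 30 eligible patients per clinic per year", "a similar SD estimate of 10.7 for absolute (kg) change in weight", and "we will have 80% power (alpha=0.05, two-sided) to detect a standardized effect size of 0.118 (ICC=0.02) to 0.121 (ICC=0.05". Table 1 gives sequences of 20, 18 and 19 clinics over four one-year periods. The Hussey-Hughes variance for a cross-sectional stepped wedge with 30 patients per clinic-period, times (1.960 + 0.842), gives detectable effects of 0.117 SD (ICC 0.02) and 0.120 SD (ICC 0.05), against the stated 0.118 and 0.121. The figure reproduces and is not disputed. In kilograms, 0.118 × 10.7 = 1.26 and 0.121 × 10.7 = 1.29.

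**2. Maintenance model.** The documents give no recording rates, so all inputs here are assumptions:
- True comorbidity prevalence π = 0.5 in both conditions.
- Probability of being recorded, s: 0.5 (SOC) vs 0.9 (PATHWEIGH), or 0.6 vs 0.8.
- No false recording.
- Log-odds of maintenance 1.4 without the comorbidity (probability 0.802).
- Comorbidity OR 0.5 (probability 0.670) or 2 (probability 0.890).
- True intervention OR 1.

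The share of true cases among patients with nothing recorded is π(1−s)/(1−πs):
- SOC, s = 0.5: 0.25/0.75 = 0.333.
- PATHWEIGH, s = 0.9: 0.05/0.55 = 0.091.

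With comorbidity OR 0.5, maintenance among the not-recorded is:
- SOC: 0.667 × 0.802 + 0.333 × 0.670 = 0.758.
- PATHWEIGH: 0.909 × 0.802 + 0.091 × 0.670 = 0.790.

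The odds ratio in this stratum is (0.790/0.210)/(0.758/0.242) = 1.20. Among the recorded it is 1. The logistic model adjusted for the recorded field averages the two:

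| Recording, SOC vs PATHWEIGH | Comorbidity OR | Adjusted OR, simulated | Adjusted OR, exact large-sample value |
|---|---|---|---|
| 0.5 vs 0.9 | 0.5 | 1.13 | 1.12 |
| 0.5 vs 0.9 | 2 | 0.89 | 0.90 |
| 0.6 vs 0.8 | 0.5 | 1.05 | 1.06 |
| 0.6 vs 0.8 | 2 | 0.97 | 0.95 |
| 0.7 vs 0.7 | either | not run | 1.00 |

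The unadjusted OR is 1 by construction. The small differences between the last two columns are simulation error.

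**3. Primary model.** Simulation with no true effect. Further assumptions: comorbidity adds 6 kg to weight level and −5, −2 or +2 kg to 6-month change; patient intercept SD 20 kg; residual SD 7.5 kg, so change SD is √2 × 7.5 = 10.6 kg; one baseline and one follow-up weight.
- *Recorded comorbidity as a main effect only.* The time by intervention estimate moves by at most 0.0003 kg. The distortion, about −0.3 to −1.1 kg, falls on the intervention main effect, which is not tested here.
- *Covariate by patient-time term added.* The interaction moves by 0.16 to 0.80 kg in either direction, that is 0.156/1.26 = 12% to 0.802/1.26 = 64% of the detectable difference.
- *Equal recording (0.7 vs 0.7).* It moves by less than 0.01 kg in every model.

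The first result is expected. A time-fixed main effect shifts all of a patient's weights equally and so drops out of within-patient change.

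These calculations use equal allocation and omit calendar period and clinic and provider effects. They show direction and rough size, not a forecast.

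**The case against.** **Comorbidities are linked, not written.** A reader might infer that PATHWEIGH writes comorbidity codes into the record. Only the overweight or obesity diagnosis is added automatically; linking may attach diagnoses already on file. Optional use dilutes any gap further. This stands: unequal capture is possible but not demonstrated.

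**The primary outcome is protected.** A reader might infer that the 6-month result is biased. Aim 1, Analysis, names no covariate by time term, and section 3 of the working shows practically no shift without one. This stands.

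**SOC patients are not shown to drop out of the fit.** A reader might infer that behaviors and goals are largely missing under SOC, so that a complete-case analysis loses control patients. The text does not say that the questionnaire is the source of those fields, SOC has its own intake form, and no complete-case rule is stated. This stands.

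**Covariate detail belongs in the SAP.** Exact look-back windows and code lists do. But the article itself fixes a candidate list and a selection rule, and together they admit unsuitable variables. This part of the objection fails.

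**Adjustment has a purpose.** Aim 1, Analysis, warns that intervention-period patients may differ systematically from control-period patients, so cutting covariates may leave real confounding. This stands as a cost of the fix.

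**Conclusion.** The point holds for the maintenance outcomes and for the covariate rule. As written, Aim 1 may adjust for fields whose completeness depends on condition, and for treatment strategy, which follows the intervention. Under assumed recording of 50-60% vs 80-90%, 50% prevalence and a comorbidity OR of 0.5 or 2, adjustment moves a true maintenance OR of 1 to about 0.89-1.13. The direction depends on whether the comorbidity hinders or helps maintenance. The bias shrinks to zero as recording becomes equal.

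The behaviors-and-goals and treatment-strategy items are explicit in Aim 1. For comorbidities and medications, confounder status is inferred from Table 3.

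The primary interaction test is at risk only if covariates interact with patient time or vary over time, and the article states neither. The kilogram shifts above should not be quoted against the primary analysis as it stands.

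This is a worthwhile, inexpensive improvement, not a flaw that undermines the trial.

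**What to change.** In Aim 1, Outcomes and Measures and Analysis:
- Limit adjustment variables to those dated before the index visit and captured the same way in both conditions. The Aim 2 rule for clinic- and provider-level mediators is a ready model for the second part.
- Use one common look-back for comorbidities and medications, for example 12 months.
- Exclude treatment strategy, and any field filled by the PATHWEIGH questionnaire or SmartSet, from models that compare conditions. They can still be described within PATHWEIGH, and treatment keeps its place as an Aim 2 mediator.

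**Cost.** A change of analysis wording; no clinical procedure changes. Some true comorbidities not coded in the look-back will be missed, and some residual confounding may remain. The stated extraction starts on March 17, 2020, so first-year SOC patients may have a shorter look-back. An earlier covariate pull would even this out but is optional.

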#### Staff workflow

Placards may be placed at the front desk of the clinics alerting patients that they may make a weight-prioritized visit if they would like medical assistance with their weight. Each clinic or provider will determine the number of weight-prioritized visits available. Once a patient schedules a weight-prioritized visit, Epic will request they complete a specified weight management questionnaire upon e-check-in prior to their visit. Medical assistants (MAs) will review provider schedules ahead of time to ensure patients complete this questionnaire prior to their visit. At the time of the patient visit, MAs will record the patient’s weight and vital signs with no other assistance required. Collectively, the workflow maximizes time for the clinician-patient conversation in the context of the Patient-Centered Medical Home [10].

#### Clinician workflow

To optimize efficiency and guide care, health care providers are encouraged to use the PATHWEIGH weight management SmartSet in Epic. A SmartSet is a documentation template used in the ambulatory setting comprised of a group of orders and other elements, such as notes, chief complaints, medications, and levels of service charges, that are commonly used together to document a specific type of visit. This SmartSet addresses the following.
Diagnosing overweight or obese patients with a BMI > 25 kg/m^2^ or > 30 kg/m^2^, respectively, recognizing these as bona fide disease states [6]Linking diagnoses for weight-related comorbidities to facilitate reimbursementPre-populating information from the patient weight management questionnaire to serve as documentation and to guide the clinician-patient discussion, and flagging weight management strategies based on guidelines from the Obesity Society [32], specifically, the discussion of lifestyle change for patients with BMI ≥ 25 kg/m^2^, consideration of medications impacting obesity as well as anti-obesity medication at BMI ≥ 30 kg/m^2^ (or BMI ≥ 27 kg/m^2^ with weight-related comorbidities) and consideration of bariatric surgery for BMI ≥ 40 kg/m^2^ (or BMI ≥35 kg/m^2^ with weight-related comorbidities)Providing options for orders that include laboratory testing, referrals, or procedures

Behavioral health professionals work alongside many of the primary care providers and are encouraged adjuncts to facilitate weight loss. Use of the PATHWEIGH tools is entirely optional for clinicians. Use may be deployed by the clinicians in advance of the visit or if they or the patient spontaneously decides to prioritize weight management. The process strongly encourages regular follow-up (usually at 4–6 week intervals and more often initially). A key advantage is that the clinician is the patient’s regular provider and will have an ongoing relationship with the patient over time and can safely manage or discontinue medications or other issues for weight-related comorbidities.

### Implementation framework and strategies

#### Conceptual framework

Implementation and evaluation of PATHWEIGH is guided by the Practical, Robust, Implementation and Sustainability Model (PRISM) [33]. RE-AIM (Reach, Effectiveness, Adoption, Implementation, and Maintenance) has often been used as a planning and evaluation framework for capturing important measures in implementation research, but it lacks measures of context and drivers of success [34–37]. PRISM was developed to address the issues of multi-level features for successful program design, predictors of implementation success, factors associated with diffusion, implementation, and maintenance [33]. The key contextual factors for examination include the interaction of system and patient levels with the intervention (includes model components of recipients and intervention), infrastructure elements related to implementation and sustainability (model element of implementation sustainability and infrastructure), and external/environmental factors (model element of external environment) and how they exert an influence on the RE-AIM outcomes.

